### Type, location, and population of the study

2.1

This study protocol follows the items of the Standard Protocol for Randomized Trials. It is an experimental study, specifically a randomized clinical trial on the autonomic HR modulation response, in which 50 volunteers with normal vision (Group i) and 50 individuals with visual deficiency (Group ii) have attended the Pedagogical Service of Support Center for People with VI (Fig. 1).

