### Data collection instruments

2.7

*First phase*: A sheet will be used to collect personal and sociodemographic data, complemented with clinical data according to the execution of medical examinations and interventions in the study participants.

Initially, it is intended to form the Group ii by searching people with VI from the Pedagogical of Support Center CAP-AC database, a public institution that exclusively provides socioeducational support services to low vision patients and the Centro de Saude Ocular (CSO), which is a private clinic of ophthalmologic care in Rio Branco City. Individuals for Group i those without VI who have good visual acuity will be invited from the CSO, seeking to match them as closely as possible with Group ii, regarding gender, age, occupation, etc.

After initial selection, volunteers will be submitted to routine clinical-ophthalmological examination, where aspects of general health will be investigated, as well as medication that may interfere with ANS, among others. Other aspects of eye health, such as visual acuity, corrective lenses, and history of ophthalmic surgery also will be evaluated.

Clinical and ophthalmological examinations that will indicate the study independent variables will be performed at the CSO, which has qualified human resources and medical equipment for anamnesis, visual acuity measurement, ocular pressure measurement, among others, with no costs for participants.

*Second phase*: In this phase, data of HRV will be collected. The protocol will be the same for both groups (Group i and Group ii). It will be divided in 3 moments of 15 minutes each: rest-intervention-recovery. After taking anthropometric measures, the participant of Group i will be given a brief rest in seated position, in a quiet environment, then the systolic, diastolic, and mean BP and HR will be measured to define a baseline condition (rest phase). Then, in the 2nd step or intervention phase, both eyes of the participant will be blindfolded with a sleeping mask that provides maximum occlusion (Fig. 5), remaining with vigilance and companionship.

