### Data analysis

2.8

Data will be analyzed using the Statistical Package for Social Science, version 22.0. Descriptive analysis will be performed for all variables. Data will be expressed as mean ± standard deviation or median (interquartile range), where appropriate. Sample distribution will be tested with the Shapiro–Wilk test. For comparison of initial and final values between groups, the unpaired Student *t* test for parametric distributions and the Mann–Whitney test for nonparametric distributions will be applied. Statistical significance will be considered at the level of *P* < .05 (or 5%).

As a risk measure, odds ratio will be calculated, adjusted, and not adjusted with their respective 95% confidence intervals. The odds ratio = 1 of lowest risk for the outcome of interest will be considered as the base category for each independent variable.

Statistically significant variables in the univariate analysis will compose the model for the multivariate analysis. In this multivariate analysis, multiple logistic regression will be used (Fig. 10).

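### Group i is recruited to resemble Group ii on gender, age and occupation, but the between-group test ignores these factors and is conservative to the extent that they predict the outcome

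*Protocol article*

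**What the plan says.** Three places in the protocol article bear on this.

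- **Section 2.1 (type, location and population)** sets the group sizes: "50 volunteers with normal vision (Group i) and 50 individuals with visual deficiency (Group ii").
- **Section 2.7 (data collection instruments)** forms Group ii first, from the support centre's database and an eye clinic. Group i is then invited from the eye clinic, "seeking to match them as closely as possible with Group ii, regarding gender, age, occupation, etc". It states no pairs, matching ratio or tolerance.
- **Section 2.8 (data analysis)** fixes how the two groups are compared at the start and at the end: "the unpaired Student *t* test for parametric distributions and the Mann–Whitney test for nonparametric distributions will be applied". The significance level is 5%, with sidedness not stated.

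The only adjusted analysis in Section 2.8 is a multiple logistic regression that yields odds ratios. Its covariates are chosen by a screen: "Statistically significant variables in the univariate analysis will compose the model for the multivariate analysis". The matching factors are not named there.

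**The concern.** Choosing Group i to resemble Group ii gives the two groups similar distributions of gender, age and occupation. Where those factors influence an outcome, the group means move together and their difference varies less from sample to sample than it would between two independently drawn groups. The unpaired t test and the Mann-Whitney test take the samples as independent. They therefore charge the comparison for variation that the recruitment has already removed.

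What is at stake is precision. The recruitment effort spent on matching earns nothing in the analysis, confidence intervals may be wider than they need to be, and a real difference between sighted and visually impaired participants is more easily missed with the same 100 people.

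The logistic regression does not repair this. It gives odds ratios rather than a difference in the continuous measurement, and whether a matching factor enters depends on its P value.

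**Working it through.** **Inputs from the article.** n = 50 per group (Section 2.1); unpaired t test or Mann-Whitney test (Section 2.8); significance level 0.05 (Section 2.8). The article gives no power, SD, effect size or correlation, so there is no figure of its own to reproduce.

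**Assumptions.** Outcome SD = 1; two-sided test; outcome correlation ρ between matched participants from 0 to 0.5; true difference 0.4 SD.

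**Step 1: standard error of the difference.**

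- Unpaired: √(2/n) = √(2/50) = 0.200.
- True value under matching: √(2(1−ρ)/n). At ρ = 0.3 this is √(2 × 0.7/50) = 0.167.
- Ratio: 1/√(1−ρ). At ρ = 0.3 this is 1/√0.7 = 1.20.

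**Step 2: real type I error of the unpaired test.** This is 2 × [1 − Φ(1.96/√(1−ρ))]. At ρ = 0.2 it is 2 × [1 − Φ(2.19)] = 2.8%.

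**Step 3: power at 0.4 SD.** The unpaired test is referred to t with 98 degrees of freedom. The paired test uses the noncentral t with 49 degrees of freedom and noncentrality 0.4/SE. At ρ = 0.3 that is 0.4/0.167 = 2.39.

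| ρ | True SE | Unpaired SE / true SE | Type I error, unpaired | Power, unpaired | Power, paired |
|---|---|---|---|---|---|
| 0 | 0.200 | 1.00 | 5.0% | 51% | 50% |
| 0.1 | 0.190 | 1.05 | 3.9% | 51% | 54–55% |
| 0.2 | 0.179 | 1.12 | 2.8% | 51% | 59% |
| 0.3 | 0.167 | 1.20 | 1.9% | 51% | 65% |
| 0.5 | 0.141 | 1.41 | 0.6% | 51% | 79% |

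With ρ = 0 the paired test is very slightly worse, because it gives up half the degrees of freedom for nothing. At a difference of 0.5 SD the two tests have equal power (71.0%) at ρ = 0.05. At ρ = 0.1 they are 71.5% and 73.3%, with a normal approximation for the unpaired figures.

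**Step 4: does the effect depend on one-to-one pairs?** A simulation of 20,000 replicates let the matching factors explain 30% of the outcome variance. The mean unpaired SE was 0.199 throughout.

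| Type of matching | True SE | Mean paired SE | Type I error, unpaired | Type I error, paired |
|---|---|---|---|---|
| Exact pairs | 0.168 | 0.166 | 2.0% | 5.0% |
| Loose pairs (matching factor correlated 0.7 within pairs) | 0.177 | 0.177 | 2.8% | 4.9% |
| Same distribution over quartile strata, no pairs | 0.173 | 0.199 | 2.4% | 2.5% |

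The unpaired SE is too large in all three rows. In the last row the paired test is no better than the unpaired one; there, only adjustment for the matching factors recovers the precision. With 0% of variance explained, the unpaired SE was correct under every kind of matching.

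**The case against.** **The matched design may be looser than it sounds.** Section 2.7 describes a best effort, on an open-ended list of factors, with no pairs defined. Equal group sizes are not evidence of pairing. Section 2.2 also limits Group i to healthy people who need no glasses, so close matching on several factors is not assured. This stands. A reader might infer a one-to-one matched design for which an unpaired test is simply the wrong test; the article does not support that. What survives is narrower: whatever similarity is achieved, the named comparison does not use the factors that created it.

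**The effect is conditional.** A reader might also infer that the standard errors of every comparison are too wide. That needs the factors to predict each outcome. The article gives no such information, and the strength would differ between outcomes. This stands too. A correlation of 0.5 is the top of the assumed range: it would need the matching factors to explain about half the outcome variance under near-exact matching.

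**The logistic screen may not drop the matching factors.** They would tend to be dropped if group were the dependent variable, but Section 2.8 refers only to an outcome of interest. Against a continuous outcome, a factor explaining 20% of variance (r = 0.447) would pass a 5% screen with n = 100 almost surely: atanh(0.447) × √97 = 4.74, and Φ(4.74 − 1.96) = 99.7%. At 10% of variance the figure is about 90%; a dichotomised outcome would lower both. So it cannot be said that the screen removes them. The reply is only that an odds ratio from that model does not replace the comparison of continuous values.

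**Such detail may sit in a fuller plan.** Whether links are recorded may well be settled in the data sheet or an analysis plan that is not shown, so a missing pair identifier is not claimed here. The choice of test, however, is stated in the article, and it is the stated test that leaves the precision unused.

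**Conclusion.** The point holds as a conditional loss of precision. To the extent that gender, age and occupation predict an outcome, the unpaired comparison overstates its standard error: by 5% at an assumed correlation of 0.1, 12% at 0.2, 20% at 0.3 and 41% at 0.5. The cost in power at an assumed 0.4 SD is about 3 to 4 percentage points at 0.1, 8 at 0.2, 14 at 0.3 and 28 at 0.5. Near zero correlation there is no cost.

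Ignoring the matching does not bias the mean difference, and the false-positive rate falls below 5% rather than rising above it. The article sets no power target, so none can be said to be missed. The stated analysis remains valid. The change is worth making because it is nearly free and works whether matching is by pair or by group.

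**What to change.** In Section 2.8:

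1. Make the main between-group comparison of each continuous outcome a linear model, with the outcome transformed where its distribution requires it. Always include group, age, sex and occupation class, whatever their univariate P values. Report the adjusted group difference with its 95% confidence interval.
2. State whether matching is individual or by frequency, and name the factors in place of the open-ended list.
3. Use the paired t test or Wilcoxon signed-rank test only if one-to-one links are actually formed and recorded, and check normality on the pair differences. Under frequency matching a paired test recovers no precision.

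**Cost.** No extra participants, and no extra measurements beyond the matching factors already needed to select Group i. The model uses a few of the 98 residual degrees of freedom: with, say, four occupation classes, 1 + 1 + 3 = 5, leaving 93. A strict pair analysis costs more: it has 49 degrees of freedom and loses a whole pair when one member is missing, which is why the adjusted model is the better main analysis.

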**Figure 9 F9:**
[figure not shown]
Data transfer.

Data collection of intervention in subjects of Group i, temporary deprived of vision, will be performed individually, on working days from 8:00 to 12:00 am, recorded in a standardized sheet (Annex 4). The venues will be discrete and isolated, which could be in the outpatient or recreation/training environment of CAP-AC and the CSO in Rio Branco.

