## Discussion

3

Overall, in 2010, out of a total of 32.4 million blind and 191 million visually impaired, 0.8 million were blind and 3.7 million were visually impaired because of diabetic retinopathy (DR), with an alarming increase of 27% and 64%, respectively, in the 2 decades from 1990 to 2010. These numbers were lower in regions with younger populations (<2% in Southeast Asia and Oceania) than in high-income regions (North America, Western Europe, and Asia) with populations relatively aged (>4%).^[18]^

Dyslipidemia and hypertension may also influence DR, although in the context of individual patients, the associations between plasma lipids, lipoproteins, and DR are not strong enough to define the risk of retinopathy. Similarly, hypertension has been associated with increased risk of RD, and some data indicate that patients may benefit from the use of antihypertensive agents. However, recent studies have shown that more intensive BP monitoring does not confer additional benefits on the progression of retinopathy compared to standard follow-up. Taken together, the optimization of systemic risk factors is clearly important; however, even hyperglycemia (as measured by HbA1c) may represent only about 10% of risk of DR, and combined hypertension and dyslipidemia can lead to <10% risk in some cohorts. Such data strongly suggest that additional unidentified factors also play critical roles in the initiation and progression of DR.^[19]^

Universality is linked to the guarantee of the right to the same level of healthcare for all Brazilians, without any discrimination. It is very relevant researching about better ways of achieving positive results, new knowledge, and products that will improve the health of the population, either with a new diagnosis or new therapeutic treatments, or even with actions aimed at promoting the health of the population.^[20,21]^ The authors intend to propose a good quality protocol in its execution, having patient safety and demonstrating reliable information for healthcare area, contributing for better health care indicators of visually impaired people.

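### Groups defined by visual status are compared without adjustment, and covariates reach the only adjusted model by univariate significance, so autonomically active medication can go uncontrolled

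*Protocol article*

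**What the plan says.** Section 2.1 of the Protocol article calls the study a randomized clinical trial and sets 50 volunteers with normal vision against 50 people with visual deficiency. Section 2.2 assigns people to these groups by visual acuity. It asks for healthy people in Group i and people in good general health in Group ii; neither diabetes nor medication is named.

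Section 2.7 plans to match Group i to Group ii as closely as possible on gender, age, occupation and the like. It also says that the clinical examination will look at general health, "as well as medication that may interfere with ANS, among others". It gives no rule for what is done with that information.

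Section 2.8 describes the group comparison: "For comparison of initial and final values between groups, the unpaired Student *t* test for parametric distributions", with Mann-Whitney as the nonparametric alternative. Significance is set at P < .05. Covariates for the adjusted analysis are chosen as follows: "Statistically significant variables in the univariate analysis will compose the model for the multivariate analysis". The model is then named: "In this multivariate analysis, multiple logistic regression will be used". The binary outcome of that model is not defined.

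**The concern.** Visual status cannot be allocated at random, so Group i against Group ii is an observational contrast and control of confounding falls to matching and analysis. The matching list does not name the factor that section 2.7 itself singles out, medication acting on the autonomic nervous system. That factor bears directly on the outcome, since HRV is the study's measure of autonomic activity.

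The analysis does not close the gap. The tests on HRV carry no covariates. The only adjusted model admits a variable on its own P value, so whether medication is controlled depends on how its association happens to fall in 100 people. With no binary outcome defined, it is not even clear that this model adjusts the HRV comparison. If drugs or diabetes are commoner among people with visual impairment, part of their effect on HRV may be credited to the impairment.

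**Working it through.** **Inputs from the Protocol article.** 50 per group (section 2.1); threshold 0.05 (section 2.8), two-sided assumed. The article gives no effect size, SD or power, so there is no stated figure to reproduce. For scale, 50 per group has 70.5% power for a standardized difference of 0.5 and 80% for 0.56.

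**Assumptions, not in the article.** The factor is 10 to 30 percentage points commoner in Group ii and lowers HRV by 0.5 to 1.0 SD. There is no true group effect.

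**Step 1: the unadjusted test.**

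- SE of the group difference in SD units = sqrt(2/50) = 0.20.
- Bias = prevalence difference × effect.
- False-positive rate = Φ(bias/0.20 − 1.96) + Φ(−bias/0.20 − 1.96).

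| Prevalence difference | Effect (SD) | Bias (SD) | Bias/SE | False-positive rate |
|---|---|---|---|---|
| 0.10 | 0.5 | 0.05 | 0.25 | 5.7% |
| 0.20 | 0.8 | 0.16 | 0.80 | 12.6% |
| 0.30 | 1.0 | 0.30 | 1.50 | 32.3% |

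**Step 2: the screening rule.** A logistic model was simulated with 50 v 50, 3,000 runs per scenario, a baseline outcome risk of 30% and no true group effect. The confounder entered only if its univariate P was below .05; this was compared with forcing it in and with leaving it out. Prevalences, confounder odds ratios and baseline risk are assumptions.

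| Prevalence, i v ii | Confounder OR | Dropped | Type I: unadjusted | Type I: screened | Type I: forced in | Median group OR: screened | Median group OR: forced in |
|---|---|---|---|---|---|---|---|
| 5% v 20% | 2 | 80% | 6.1% | 5.3% | 5.1% | 1.09 | 1.02 |
| 5% v 20% | 3 | 60% | 6.9% | 5.3% | 5.2% | 1.09 | 0.99 |
| 5% v 20% | 4 | 41% | 7.8% | 4.7% | 4.6% | 1.06 | 1.00 |
| 10% v 30% | 2 | 73% | 5.5% | 4.5% | 4.8% | 1.09 | 0.99 |
| 10% v 30% | 3 | 42% | 8.4% | 5.3% | 5.5% | 1.07 | 1.00 |
| 10% v 30% | 4 | 22% | 11.5% | 5.3% | 5.3% | 1.05 | 1.01 |
| 10% v 40% | 2 | 69% | 7.9% | 5.1% | 4.8% | 1.09 | 0.99 |
| 10% v 40% | 3 | 37% | 12.5% | 5.1% | 4.6% | 1.07 | 0.99 |
| 10% v 40% | 4 | 18% | 17.0% | 5.4% | 5.0% | 1.04 | 1.00 |

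The simulation error on a 5% rate is about sqrt(0.05 × 0.95/3000) = 0.4 points, so screened and forced-in type I error are not distinguishable here.

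**Step 3: reading the two together.** The screen often loses a real confounder: 69% to 80% of runs at OR 2 and 37% to 60% at OR 3. In the runs where it is lost, the median group OR is 1.09 to 1.20 over all nine scenarios, although the truth is 1. Over all runs the shift is small, because the confounder is dropped mainly when its observed effect is weak. Inflated error appears when there is no adjustment at all, which is how section 2.8 compares the groups.

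**The case against.** Several counter-arguments have force.

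- **The screen is not the main source of harm.** A reader might attach the 6% to 32% to the selection rule, or infer that the rule makes confidence intervals too narrow. The simulation supports neither: screened type I error was 4.5% to 5.4%. The range belongs to the unadjusted test only.
- **Diabetes.** A reader might infer that diabetic eye disease is recorded and knowingly admitted. The article does not say so. Diabetic retinopathy appears only in the Discussion, as global epidemiology. The health criterion in section 2.2 may exclude such patients, and the eligibility figure is not shown. The Discussion's figures also suggest a small share: 0.8/32.4 = 2.5% of blindness and 3.7/191 = 1.9% of visual impairment. At about 2 points and 0.5 to 1.0 SD the bias would be 0.01 to 0.02 SD and the false-positive rate 5.0% to 5.1%. Those figures do not give the prevalence of diabetes or of medication use in Group ii, so they do not bound the whole problem.
- **Matching.** It should reduce confounding by gender, age and occupation. It is approximate, and neither medication nor diabetes is among the factors named.
- **Time of day.** Section 2.7 gives a morning window for "subjects of Group i, temporary deprived of vision, will be performed individually, on working days from 8:00 to 12:00 am", and a reader might infer that Group ii is recorded at other hours. The same section says twice that both groups follow the same protocol, so a planned difference is not established.
- **Detail left to an analysis plan.** A full covariate list often is. Here, however, section 2.8 states a selection rule, and a later plan could not force in a non-significant confounder without departing from it.

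**Conclusion.** The point stands in this form: the comparison is non-randomized, the tests on HRV are unadjusted, and the stated entry rule cannot guarantee control of a factor that the article itself flags. Confidence is high on the rule and on medication. It is moderate on diabetes, where all that can be said is that the article does not address it beyond a general health requirement.

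The size rests on assumptions. Across the assumed imbalances and effects, the false-positive rate of the unadjusted test runs from barely above nominal to about one in three; the upper end needs a 30-point imbalance and a full SD effect together. The screening rule costs modest bias in the odds ratio and no visible type I error. This is an improvement that should be made, not a flaw that invalidates the study.

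**What to change.** In section 2.8, delete the univariate screening rule. Add a group comparison of HRV from a regression model whose covariates are fixed in advance and kept whatever their univariate P values: age, sex, BMI, autonomically active medication (yes/no) and diabetes status (yes/no). Add a sensitivity analysis that repeats the comparison without participants who use such medication or have diabetes.

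In section 2.7, add diabetes status to the data collection sheet. The session glucose readings do not supply it.

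The cost is a few degrees of freedom, one added data item and some rewording. Medication and anthropometry are already planned; BMI needs height and weight to be among the anthropometric measures, which the article does not list.

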### Intervention

2.5

Liao et al^[14]^ studied 2 groups with 20 patients each, performing a 30-minute exercise program of electric bicycle and a 5-minute cooling during the treatment of hemodialysis (HD) in the renal unit. The exercise was performed under supervision of a physician and a nurse specialized in rehabilitation. This protocol was adapted to be carried out with 2 groups of 50 people each. We also modified the time for the accomplishment of activities, they will be developed in 45 minutes, split in 3 periods of 15 minutes each. Times were defined as rest, intervention, and recovery. The execution will be supervised by a researcher, an ophthalmologist, a professional physical educator, a nurse, a student, and a secretary.

Marques et al^[15]^ measured exercise intensity by using the Borg rating of perceived exertion scale. In our study, patients will perform activities without load prescription. In the study by Raimundo et al,^[16]^ the subjects walked on a treadmill for aerobic exercises split into 5 minutes of warm-up and 25 minutes of exercise, reaching 50% to 70% of their maximal HR. Morais et al^[17]^ used in its protocol in patients in HD, aerobic exercise of cyclical movements of the lower limbs with 45% to 60% of intensity of its HR maximum.

Morais et al^[17]^ performed aerobic exercises with a total time of 30 minutes, 3 times a week for 3 months. The subjects were instructed to remain with arms extended normally in the extension of the chair next to the body, accommodated in the best possible way. The lower limbs that were the most active part in the exercise performed a constant rotation (pedals) throughout the aerobic exercise in the mechanical cycle ergometer for lower limbs. Patients will be encouraged to increase their intensity according to individual capacity, respecting the principle of biological individuality.

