**Figure 6 F6:**
[figure not shown]
Educational toys.

At each stage of 5-minute intervention activities, the patient will be monitored for their systolic and diastolic HR and level of blood glucose.

In the 3rd phase called recovery with a duration of 15 minutes, the participants will sit relaxed and resting, continuing to monitor the collection of autonomic cardiac activity through the HRV.

Participants of Group ii, after verifying their anthropometric measures, will be submitted to the same protocol of Group i.

Measurements include systolic blood pressure, DBP, mean arterial pressure, HR, and blood glucose level.

The HR monitoring for further analysis of HRV will be obtained by an HR receptor RS800CX, Polar Electro, Finland. This device was validated to locate the heart beat for HRV analysis (Fig. 7). At the appropriate moment for collection during the estimated 45 minutes of evaluation, the strap will be placed on the chest of volunteers and the HR receptor (Fig. 8), which is an equipment previously validated for HR reception, beat and use these data for HRV analysis. The receiver temporarily stores the data that will then be processed on computers.

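### Section 2.8 lets univariate P < .05 choose the terms of the logistic model, with no fixed set and no limit, so the odds ratios of selected variables are biased away from 1 on average and the model can be overfitted if many related candidates pass

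*Protocol article*

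**What the plan says.** The protocol article, section 2.8 (Data analysis), sets the rule for building the model: "Statistically significant variables in the univariate analysis will compose the model for the multivariate analysis". It then names the model: "In this multivariate analysis, multiple logistic regression will be used". The significance level is 5%. The risk measure is the odds ratio, unadjusted and adjusted, with 95% confidence intervals. The category of lowest risk "will be considered as the base category for each independent variable", so a variable with k classes uses k − 1 coefficients.

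Sections 2.1 and 2.5 fix the size of the study; section 2.5 has it "carried out with 2 groups of 50 people each".

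Section 2.7 (Data collection instruments) indicates where the model variables come from: "Clinical and ophthalmological examinations that will indicate the study independent variables" are done at the eye clinic. It mentions medication acting on the autonomic nervous system, visual acuity, corrective lenses, eye surgery and ocular pressure. It also mentions sociodemographic data, and gender, age and occupation as matching factors. Later in the same section: "Measurements include systolic blood pressure, DBP, mean arterial pressure, HR, and blood glucose level". The article does not say whether these last measurements are candidates for the model. It names neither the binary outcome nor its expected frequency.

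**The concern.** Under the stated rule the data decide both which terms enter and how many. Two separate problems can follow.

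1. **Selection.** A variable enters only if its univariate estimate is large enough to be significant. The same data then supply its adjusted odds ratio. Among variables that pass, overestimates are over-represented, so the reported odds ratios lie too far from 1 on average. Variables with no effect that pass by chance appear as risk factors.
2. **Model size.** With at most 50 people in the smaller outcome class, a model with many coefficients gives maximum-likelihood odds ratios that are biased away from 1, with intervals that cover too rarely. Related candidates tend to be significant together. Systolic, diastolic and mean pressure are the obvious example, should they be candidates, because mean pressure is normally calculated from the other two.

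The adjusted odds ratio is the article's declared risk measure, so part of its size could come from the model-building rule.

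**Working it through.** **No figure to reproduce.** The article gives 50 per group without inputs, and no model size.

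**Inputs from the article.** n = 50 + 50 = 100 (sections 2.1 and 2.5); entry at P < .05 with no limit (section 2.8; two-sided assumed). **Assumed, because not given:** number of candidates, their correlation, true effects and outcome split.

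**Step 1. People per coefficient.** Smaller outcome class m divided by number of coefficients k.

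| m | k = 3 | k = 5 | k = 10 | k = 20 |
|---|---|---|---|---|
| 50 (the maximum) | 16.7 | 10.0 | 5.0 | 2.5 |
| 30 | 10.0 | 6.0 | 3.0 | 1.5 |
| 20 | 6.7 | 4.0 | 2.0 | 1.0 |

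At the usual guide of 10 per coefficient, the limit is 5 terms for a 50:50 outcome, 3 for 30:70 and 2 for 20:80.

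**Step 2. Chance that at least one of K independent null variables passes.** 1 − 0.95^K gives 23% for K = 5, 40% for K = 10 and 64% for K = 20.

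**Step 3. Effect of selecting and estimating in the same data.** Simulation with n = 100 and K = 5, 10 or 20 standardised candidates, of which 2, 3 or 5 have a true odds ratio of 1.50 per SD. Each is screened at P < .05, then all selected variables are fitted together. The table shows the geometric mean adjusted odds ratio of selected true variables.

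| Outcome split | Uncorrelated | Correlation 0.3 |
|---|---|---|
| 50:50 | 1.84–1.86 | 1.57–1.68 |
| 30:70 | 1.92–1.95 | 1.62–1.75 |
| 20:80 | 2.07–2.12 | 1.64–1.88 |

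For comparison, the model with all 5 candidates pre-specified (2 true effects, uncorrelated, 50:50) gives 1.58, against 1.86 after screening. On the log scale, ln 1.86 / ln 1.50 = 0.621 / 0.405 = 1.53, a 53% inflation, and ln 1.58 / ln 1.50 = 0.457 / 0.405 = 1.13, or 13%. The effect is one of weak associations: with a true odds ratio of 2.50 and the same 5 candidates, the screened model gives 2.68 and the full model 2.71.

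**Step 4. How many terms enter.** In the same simulations, uncorrelated candidates let in 0.8 to 2.7 terms on average. At a 50:50 outcome, fewer than 10 people per term occurred in 0–8% of runs. With correlation 0.3 and K = 10 to 20, 3.4 to 13.7 terms entered on average, and fewer than 10 per term occurred in 53–99% of runs across the three splits.

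**Step 5. Effect on the odds ratio for visual status, if that term is kept in the model.** Simulation with 50 per group, true odds ratio 3, about half with the outcome, and yes/no covariates with prevalence 0.3 in one group and 0.4 in the other. Half of the covariates have log odds ratio 0.5. The covariates are screened at P < .05; counts include the group term.

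| Candidate coefficients | Mean number entering | Inflation of log OR | 95% CI coverage |
|---|---|---|---|
| 14, unrelated | 3.0 | 14% | 94% |
| 20, unrelated | 3.9 | 17% | 94.5% |
| 28, unrelated | 5.1 | 26% | 92% |

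Part of this inflation is confounding by covariates that missed the screen, not model size. With 20 to 28 candidates correlated at 0.3, about 13 to 21 terms entered and inflation was 23–57%, against about 15% for a fixed five-term model. As odds ratios, 3^1.23 = 3.9 and 3^1.57 = 5.6, against 3^1.15 = 3.5.

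**The case against.** The best defence is that the screen itself keeps the model small. A reader might infer from the long list of collected variables that 20 or more coefficients will be fitted. If every candidate is forced into the Step 5 set-up with unrelated covariates, the log odds ratio is inflated by 38% at 20 coefficients and by 85% at 28, with 83% coverage at 28. The documents do not support applying those figures here, because section 2.8 admits only significant variables. Under that screen about 3 to 5 terms entered. Model size depends directly on the screening, so it cannot be said that overfitting occurs however the variables are chosen. This part of the defence stands.

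It also stands that the candidate list is not given. The pressures, heart rate and glucose are described as measurements, not as covariates. Visual acuity defines the groups, and gender, age and occupation are matching factors. The outcome is unnamed. If visual status were itself the modelled outcome, Step 5 would not apply, although Step 3 would.

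Ten people per coefficient is a rule of thumb. In the unscreened runs, 10 coefficients gave 94% coverage, the same as 5. It should guide the size of the model, not act as a sharp boundary.

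It can be said that such details belong in an analysis plan that is not shown. That does not answer the point. The article does not leave the choice of terms open; it states a rule, and the rule is a poor one. A limit on terms alone would not cure it either, since the selection effect in Step 3 appears with very few terms.

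**Conclusion.** The point holds in two parts of different strength.

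- **Selection bias follows from the rule as written.** It is an average tendency away from 1. In the settings tried, a true odds ratio of 1.50 became 1.57 to 2.12 among selected variables, and 1.86 against 1.58 in the direct comparison with a pre-specified model. It is large for weak associations and adds nothing visible for strong ones (2.50).
- **Overfitting is conditional.** It is minor if few terms pass the screen. It becomes material if candidates are many and related: roughly 20–60% on the log odds ratio for visual status with 20 to 28 candidates correlated at 0.3. A less even outcome split lowers the number of terms the data can carry.

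A reader might go further and conclude that the adjusted odds ratios will certainly be overfitted and too large. The documents do not support that. They state neither the number of candidates, nor the correlation, nor the outcome split. Protective odds ratios would tend to be too small, and any single estimate can err either way. Apart from n = 100 and the 5% level, every simulation input is an assumption, so the figures are orders of magnitude.

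**What to change.** In section 2.8, replace the univariate-significance rule with a short list of adjustment variables chosen on subject-matter grounds and fixed before the data are seen. Size the list to the smaller outcome class, at about one coefficient per 10 people as a guide: about 5 coefficients at most for a 50:50 outcome and fewer otherwise, counting each dummy variable as one. Include at most one blood-pressure variable. If more terms must stay, fit the model by Firth's penalised likelihood with profile-likelihood 95% intervals.

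The cost is one or two sentences, with no change to recruitment, procedures or data collection. The downside is that fewer variables are adjusted for in one model, which can leave some confounding by those omitted, or that an SPSS add-on is needed for the penalised fit.
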